### Participant timeline {13}

Our trial establishes the following timeline:

### Sample size {14}

#### Sample size assessments

##### Hypotheses

Statistically significant differences between groups are not expected at baseline (t=0). Our primary hypotheses concern the difference in differences (DIDs) at 6 months and 12 months, where we expect both clinically meaningful and statistically significant differences. Sample size assessments for the study are based on demonstrating 80% power to test the primary hypotheses in Aim 1.

Denote by *Y*_*hit*_ an outcome assessed at time *t* in the *i*-th patient in the *h-*th practice team. Generally, outcomes are assessed at baseline and at 2 additional time-points 6 and 12 months. We formulate our test of hypothesis using a generalized linear (mixed) model (GLMM) for the expected response: *μ*_*hit*_ = *E*(*Y*_*hit*_| **x**_*hit*_, **b**_*hi*_)where **x**_*hit*_are patient characteristics and **b**_*hi*_ are random effects to capture serial correlation within participant measures and clustering.

Minimally, let $${\mathbf{x}}_{hit}^{\prime}\beta ={\beta}_{0}+{\beta}_{1}{z}_{1}+\left({\beta}_{21}{t}_{1}+{\beta}_{22}{t}_{2}\right)+{z}_{1}\times \left({\beta}_{31}{t}_{1}+{\beta}_{32}{t}_{2}\right)$$where *z*_1_is the indicator for group 1 with group 2 as referent, 2 indicators *t*_1_,*t*_2_, for time with baseline as referent and group by time interactions. Interpretation of parameters is shown in Table 3.

**Table 3 Tab3:** Exemplar parameter interpretation in model

Study Arm	Time			Change from t=0	
	t=0	t=6m	t=12m	At t=6m	At t=12m
GROUP2	*β*_0_	*β*_0_ + *β*_21_	*β*_0_ + *β*_22_	*β*_21_	*β*_22_
GROUP1	*β*_0_ + *β*_1_	*β*_0_ + *β*_1_ + *β*_21_ + *β*_31_	*β*_0_ + *β*_1_ + *β*_22_ + *β*_32_	*β*_21_ + *β*_31_	*β*_22_ + *β*_32_
DIFF	*β*_1_	*β*_1_ + *β*_31_	*β*_1_ + *β*_32_	DID=*β*_31_	DID=*β*_32_

Hence the net difference (DID) at 12 month is *β*_32_. Our study is powered to test the hypotheses: (a) *H*_0_ : *β*_31_ = 0, (b) *H*_0_ : *β*_32_ = 0and jointly (c) *H*_0_ : (*β*_31_, *β*_32_) = 0. Two other design features are a serial correlation *ρ*_*W*_ between repeated measures over time, an intra-class correlation (ICC) *ρ* for clustering within practice team. We obtained plausible inputs for *r* and *ρ* from the literature and our own experiences [45–48]. In community intervention studies *ρ* is small (we use 0.002) but *ρ*_*W*_ is much larger (we use 0.30). The hypothesized adherence rates at 0, 6, and 12 months are 0.40, 0.42, and 0.42 in group 2 and projected to be 0.40, 0.62, and 0.65 in group 1. With 9 teams in the combined intervention group, 8 in the text alone group, and at least 22 patients in each team, the power to detect differences between groups at 6 months and 12 months is 80.8% and 90.4%, respectively. The power to detect the DID at 6 months is 71.4% and 83.1% at 12 months. Thus, our target sample size is a total of 320 patients. Because some attrition is expected over the 4-year period, we will recruit a total of 378 patients to account for attrition of 10% in YR=1, another 4% in YR=2, and another 2% in YR=3.

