## Introduction

### Background and rationale {6a}

The objective of this study is to decrease cardiovascular disease (CVD) risk for minority and low-income adults with type 2 diabetes (T2DM) by improving medication adherence. Despite nationwide improvements in CVD mortality and morbidity [1], CVD deaths in patients with T2DM are 2–4 times higher than among those without T2DM [2, 3]. A key contributor is medication non-adherence. Twenty-one to 42% of T2DM patients do not take blood sugar, blood pressure (BP), or statin medications as prescribed [4], contributing to increased morbidity and mortality [5]. Treatment and prevention regimens are complex, requiring innovative approaches to extending support beyond face-to-face clinic visits. Mobile health (mHealth) interventions hold promise as a scalable support strategy. However, research increasingly suggests that mHealth alone may not change behavior enough to improve health outcomes [6, 7]. In our pilot study to improve CVD care for patients with T2DM, we found that text messaging alone did not significantly improve patient activation, self-management, or medication adherence over 4 months. However, text messaging plus enhanced patient-provider communication in the Office-Guidelines Applied to Practice (Office-GAP) Program improved adherence to refills and medications compared to text messaging alone at 4 months [8].

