## Trial design {8}

### Design

Our trial design is a pragmatic cluster-randomized trial of the test of equality between two groups. We test for equality of effects in two parallel intervention groups (1) Office-GAP + Texting and (2) Texting only, at 6 and 12 months and for change from baseline. The null hypothesis of all two-sided tests is the equality of effects between the two intervention groups. This pragmatic cluster-randomized trial randomizes 17 practice teams to two experimental groups: intervention (group 1): Office-Gap + Texting; control: Texting only (group 2). We plan to enroll at least 22 patients per team, with the target of having 320 evaluable patients for analysis. Because intact teams are randomized to treatment condition, and not individual patients, statistical analyses of outcomes in patients require accounting for intra-cluster correlation (“between subjects”) and serial correlation (“within subjects”) in repeated measures at baseline, 6 months, and 12 months.

Two theoretical frameworks guided our intervention development, measures, and proposed analysis. The first, Self Determination Theory [14–16], suggests that effective interventions need to encourage patients to articulate their own values and goals (autonomy), agree that recommended behaviors correspond with these intrinsic values and goals (autonomous motivation) and have confidence in their ability to execute the targeted behaviors (competence), and second, Social Cognitive Theory [17, 18], which builds on the importance of understanding the quality of a health decision and of developing intrinsic motivation to change behaviors. It emphasizes patients’ self- efficacy in their ability to execute specific tasks (such as medication taking and involvement in treatment decision-making). Enhancing self-efficacy improves physiologic outcomes [12] and functioning [19]. We propose an intervention involving three interactions, forming a positive feedback loop (Fig. 1) [8].

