### Interventions

#### Explanation for the choice of comparators {6b}

The comparators in this trial are clusters in which we implement a shared-decision making protocol consisting of a group visit in which patients learn tools to increase their skills and engagement in their care (“patient activation”) followed by a checklist used by providers, and patients to guide discussions during provider visits (the Office-GAP protocol) plus text messaging or text messaging alone. These options represent our approach to implement shared-decision making with text messaging as a mechanism of reinforcement in the Office-GAP group compared to text messages without a shared decision-making intervention. In our pilot study, patients’ medication adherence improved significantly with both Office-GAP + text messaging and with text messaging after four months. In the current study, we extend the intervention to 1 year to evaluate the impact of the arms on both medication adherence and cardiovascular risk score.

We hypothesize that the combination of Office-GAP plus text messaging for reinforcement will produce significant improvement in cardiovascular risk scores over 12 months. We also hypothesize that text messaging will improve patients’ cardiovascular risk at 3 and 6 months but will produce less improvement over 12 months than Office-GAP + text messaging. This hypothesis reflects our view that text messages are most valuable as reinforcement for a care plan established by the patient and provider through shared decision-making rather than as a substitute for a care plan.

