## Statistical methods

### Statistical methods for primary and secondary outcomes {20a}

#### Statistical analysis

Medication adherence will be assessed in individual patients by eCAP monitoring. Hypotheses will be tested at 6 months and 12 months.Tests are two-tailed at 5% level of significance. We compare group 1 patients to group 2 patients at baseline using, as appropriate, ANOVA-F-tests, chi-square tests, and non-parametric tests to assess equivalence of potentially confounding physiological and contextual patient characteristics. If substantive differences are found, they will be adjusted for in subsequent analyses by regression techniques, guided by the degree of dissimilarity rather than strict statistical significance [63]. Equivalence between the groups will be assessed on age, gender, education, race/ethnicity, use of statins, b-blockers, aspirin, and ACE1/ARB, blood sugar and lipid values, and team factors such physician experience.

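### The four stated power figures, as labelled, do not follow from the stated inputs, and they are attached to 22 patients per team (374) although the target drawn from them is 320 evaluable

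*Protocol article*

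**What the plan says.** All references are to the protocol article.

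- **Aim of the calculation** (Sample size, Hypotheses): "Sample size assessments for the study are based on demonstrating 80% power to test the primary hypotheses in Aim 1". The same paragraph names the DIDs at 6 and 12 months as the primary hypotheses.
- **Inputs** (same section): adherence at 0, 6 and 12 months of 0.40, 0.42 and 0.42 in group 2 and 0.40, 0.62 and 0.65 in group 1. The ICC "is small (we use 0.002") and the serial correlation is 0.30. There are 9 and 8 teams.
- **Test** (Statistical analysis): "Tests are two-tailed at 5% level of significance".
- **Result**: "at least 22 patients in each team, the power to detect differences between groups at 6 months and 12 months is 80.8% and 90.4" per cent for the group difference, and 71.4% and 83.1% for the DID.
- **Conclusion drawn**: "Thus, our target sample size is a total of 320 patients", raised to 378 for attrition.
- **Trial design, Design**: "We plan to enroll at least 22 patients per team, with the target of having 320 evaluable patients for analysis". Here 22 per team is what is enrolled and 320 is what is analysed.
- **Pilot evidence on texting alone**: the Background says that "text messaging alone did not significantly improve patient activation, self-management, or medication adherence over 4 months". The section on the choice of comparators says that "medication adherence improved significantly with both Office-GAP + text messaging and with text messaging after four months".

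**The concern.** The paragraph gives every input to the power calculation except the outcome variance, and that is bounded because adherence is a fraction between 0 and 1. The result can therefore be checked, and it does not check.

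The cluster size is also inconsistent. The power sentence uses the enrolment figure of 22 per team, while the sample size concluded from it is the post-attrition 320.

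The trial rests its size on this paragraph. As it stands, a reader cannot tell whether power for the primary contrast at 6 months is about 71% or above 80%, or whether 0.002 is the ICC that was used. The printed 71.4% misses the section's own 80% aim, and the text does not comment on it.

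The control path from 0.40 to 0.42 assumes that texting alone does almost nothing. One of the two pilot statements supports that and the other contradicts it.

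**Working it through.** **Inputs.** Rates, ICC 0.002, serial correlation 0.30 and 9 + 8 teams come from the sample size section; two-sided 5% comes from Statistical analysis. The variance is not stated. I take p(1−p), the largest variance a [0, 1] outcome with mean p can have, so the computed power is a lower bound in this respect.

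**Sample sizes.** 17 × 22 = 374 (198 + 176). 320/17 = 18.8 per team (169.4 + 150.6). The attrition step is right: 378 × 0.90 × 0.96 × 0.98 = 320.1.

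**Design effect**, 1 + (m − 1) × 0.002:
- m = 22: 1 + 21 × 0.002 = 1.042
- m = 18.8: 1 + 17.8 × 0.002 = 1.036

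**Group difference.** SE² = design effect × [p1(1−p1)/n1 + p2(1−p2)/n2]. At 6 months with 374:
- SE² = 1.042 × (0.2356/198 + 0.2436/176), so SE = 0.0518
- 0.20/0.0518 = 3.86
- Power is 97.1% (normal) or 95.0% (t, 15 df = 17 teams − 2)

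**DID.** The per-patient variance in each arm is v0 + vt − 2 × 0.30 × √(v0·vt), with the same design effect. This is conservative, because a constant team effect cancels in a DID. At 6 months with 374:
- The variances are 0.3329 and 0.3385, so SE = 0.0613
- 0.20/0.0613 = 3.26
- Power is 90.4% (normal) or 86.2% (t)

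**All four figures, %:**

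| Contrast | Stated | 374, normal | 374, t 15 df | 320, normal | 320, t 15 df |
|---|---|---|---|---|---|
| Difference, 6 months | 80.8 | 97.1 | 95.0 | 94.8 | 91.7 |
| Difference, 12 months | 90.4 | 99.4 | 98.7 | 98.6 | 97.2 |
| DID, 6 months | 71.4 | 90.4 | 86.2 | 85.7 | 80.8 |
| DID, 12 months | 83.1 | 96.5 | 94.0 | 93.8 | 90.4 |

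Against 374, the basis the sentence names, the stated figures are low by 9.0 to 19.0 points (normal) or 8.3 to 14.8 points (t).

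**Can the missing variance explain it?** No. To obtain 80.8% and 90.4% for the group difference, the SD would have to be about 0.62–0.67 on 374 or 0.58–0.62 on 320. The maximum for a [0, 1] outcome is 0.5.

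**Can another method explain it?** Pooled variance, the logit scale, a continuity correction and other totals were tried. No two-sided 5% version of the group difference came within 2 points of the stated pair.

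**What does match.** The last column gives 80.77% and 90.40% for the DID at 320. To one decimal this is the pair printed for the group difference. The pair printed for the DID is not reproduced on the stated inputs. The nearest versions change one of them: serial correlation 0 (320, normal: 71.7/83.3) or alpha 0.025 (320, t: 70.2/83.0).

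**Pilot statements.** Both describe adherence with texting alone after four months in the authors' pilot. One reports no significant improvement and the other reports a significant one. The document does not say that they refer to different measures or different pilots.

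**The case against.** The strongest reply is that the match at 320 points to a clerical fault. On this view the calculation was done on 320 with an ICC of 0.002, the DID result was labelled as the group difference, and the enrolment cluster size slipped into the sentence. The trial would then be adequately sized: at 320 the stated inputs give DID power of 80.8–85.7% at 6 months and 90.4–93.8% at 12 months, at or above the aim. On the logit scale with 15 df, the 6-month figure is about 79%.

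Much of this stands, and it rules out several stronger readings that a reader might infer:

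- **That power was computed on 374.** The sentence is worded for 374, but neither stated pair reproduces there, so the number actually used is unknown.
- **That the true ICC must be about 0.025–0.046.** That range reproduces the stated figures only if both the 374 and the labels are correct. One pair is matched with 0.002 at 320.
- **That neither DID reaches 80% at 320.** This would require scaling the printed figures down from 374, a basis on which they do not reproduce.
- **That the pilot contradiction shows the effect to be overstated by a known amount.** The comparator section gives no size for the improvement, so no power loss can be computed from it.

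The reply does not rescue the paragraph. If 80.8/90.4 is the DID, then both labels and the pair 71.4/83.1 are wrong. If the labels are right, the ICC or another input is misreported.

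A further reply is that a condensed article may leave a variance statement or sensitivity table to the full protocol. That is fair, and a sensitivity table is optional. Printed figures that disagree with the inputs beside them are a different matter.

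**Conclusion.** The point holds as an error in the text. On the stated inputs, none of the four power figures is right for the contrast it is attached to, on either 374 or 320. The power sentence and the target drawn from it also use different cluster sizes, 22 and about 18.8. Mislabelling is the likeliest explanation but is not proven.

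As printed, a primary hypothesis, the 6-month DID, has 71.4% power against the section's own 80%. That shortfall is in the document's own figure and does not come from the 374-versus-320 mismatch. Underpowering is not shown: on the stated inputs, 320 evaluable patients suffice on the proportion scale. That reassurance depends on 0.002 being the ICC actually used.

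The result assumes p(1−p) variance, the stated correlations, and a normal or 15-df t reference. The conflict between the two pilot statements is real and separate. It bears on whether 0.40 to 0.42 is a defensible control path.

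**What to change.** 1. Recompute power at 320 evaluable patients, about 18.8 per team, and use that cluster size as the stated basis in place of 22 per team.
2. Replace the four figures, naming for each the contrast (group difference or DID) and the time point.
3. State the ICC, outcome variance and degrees of freedom actually used. If the ICC was not 0.002, correct it.
4. If the 6-month DID still falls below 80% after correction, say so beside the 80% aim.
5. Reconcile the Background and comparator sections on whether texting alone improved adherence in the pilot, and cite the corrected statement as support for the control path.

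The cost is a few hours of computation and a rewritten paragraph. Enrolment, the attrition allowance and the analysis model are unaffected. The corrected figures may turn out less favourable if a larger ICC was in fact used.

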### Outcomes {12}

All data will be collected at baseline, 6 months, and 12 months (Table 2). Our primary outcome is medication adherence measured using eCAP electronic monitoring and self-report. Secondary outcomes are (a) diabetes-specific 5-year CVD risk as measured with UK Prospective Diabetes Study (UKPDS) Engine score; (b) provider engagement as measured by CollaboRATE Shared-Decision Making measure; and (c) patient activation measures (PAM).

**Table 2 Tab2:** Measures table

Variables	Instruments	Methods	Analysis	Time
**Knowledge and attitude about patient-centered care, SDM, use of DSTs**	**Pre and post survey of providers** **Semi-structured interviews**	**90 min. CME interactive orientation sections with providers and exit interviews**	**Descriptive pre-post analysis** **Thematic analysis of transcribed interviews using Dedoose**	**Pre and post physician education** **End of study**
**Medication adherence**	**Medication Events Monitoring Systems ( eCap).** **Cronbach’s alpha=.0.85** **ARMS Survey**	**eCap upload to BRIC** **RA will administer form to patient pre/post intervention to evaluate treatment medication adherence**	**Linear or generalized linear mixed effects model and Beta regression to evaluate changes over time for groups 1 and 2**	**Baseline, 6 and 12 months**
**Patient Activation Measure Scores/Level**	**Patient Activation Measure (PAM) Cronbach’s alpha=.91**	**RA administers form to patient pre and post intervention**	**Linear or generalized linear mixed effects model for change overtime for groups 1 and 2**	**Baseline, 6 and 12 months**
**Self-Efficacy Scores**	**Stanford 6-Item Self Efficacy Scale** **Summary DM Self-Activities Measure (SDSCA)**	**RA administers form to patient pre and post intervention to evaluate change in self-efficacy**	**Linear or generalized linear mixed effects models for change over time for groups 1 and 2**	**Baseline, 6 and 12 months**
**Rate of use of aspirin/antiplatelets, beta-blockers, ACEI/ARBs, cholesterol assessment and treatment, DM medications**	**PAI agreement in chart** **Patient medication list** **Patient medical record** **Texting log**	**Chart audits to compare the rate of use of aspirin/antiplatelets, beta-blockers, ACEI, cholesterol assessment and treatment of DM**	**Linear or generalized linear mixed effects model for change overtime for groups 1 and 2**	**Baseline, 6 and 12 months**

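### The plan promises 80% power for its primary hypotheses but reports 71.4% for one of them, its power figures do not follow from its inputs, and it does not say which result decides success

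*Protocol article*

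**What the plan says.** Protocol article, Sample size {14}, Hypotheses, defines the target: "Our primary hypotheses concern the difference in differences (DIDs) at 6 months and 12 months". It sets the criterion: "Sample size assessments for the study are based on demonstrating 80% power to test the primary hypotheses in Aim 1". The same section then lists three null hypotheses, introduced by "Our study is powered to test the hypotheses": no DID at 6 months, no DID at 12 months, and neither, tested jointly.

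Two pairs of powers follow. For point-in-time comparisons, "the power to detect differences between groups at 6 months and 12 months is 80.8% and 90.4%, respectively". For the primary hypotheses, "The power to detect the DID at 6 months is 71.4% and 83.1% at 12 months". No power is given for the joint hypothesis. The section then concludes that 320 evaluable patients are needed and 378 will be recruited.

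On the measure, Outcomes {12} says: "Our primary outcome is medication adherence measured using eCAP electronic monitoring and self-report". The Primary outcome text identifies the self-report instrument as the ARMS scale. Statistical analysis {20a}, however, names only eCAP monitoring where it says hypotheses are tested at 6 and 12 months, and Outcome assessment builds the analysed index (MAI) from eCAP data alone. On the significance level: "Tests are two-tailed at 5% level of significance".

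**The concern.** The criterion and the result cannot both stand. If the primary hypotheses are the two DIDs and the criterion is 80%, then 71.4% at 6 months fails it, and 320 does not follow. A reader who sees 80.8% and 90.4% first may think the criterion is met, but those figures are labelled as a different contrast.

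H1 in Objectives {7} claims improvement at 6 and 12 months, and the Hypotheses text expects significant differences at both. The natural reading is therefore that both DIDs must succeed, and power for that is lower than for either alone.

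The decisive result is also not fixed. ARMS is primary in the outcome text and absent from the testing text, and nothing says what follows if one time point succeeds and the other does not. In an open-label trial this should be settled before outcome data are examined.

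**Working it through.** **1. Inputs, all from Sample size {14}.** Group 2: "The hypothesized adherence rates at 0, 6, and 12 months are 0.40, 0.42, and 0.42 in group 2". Group 1 rates: 0.40, 0.62 and 0.65. ICC 0.002; serial correlation 0.30; 9 and 8 teams; 320 evaluable patients. Two-sided 5%, from Statistical analysis {20a}.

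**2. Attrition reproduces.** 378 × 0.90 × 0.96 × 0.98 = 320.1.

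**3. DID power from the stated inputs.** No SD is given, so I assume the variance of a proportion.
- Variance per arm = [p0q0 + p1q1 − 2 × 0.30 × √(p0q0 × p1q1)] / n. The design effect multiplies it.
- n1 = 320 × 9/17 = 169.4; n2 = 320 × 8/17 = 150.6; patients per team = 320/17 = 18.8.
- Design effect = 1 + 17.8 × 0.002 = 1.036.
- Bracketed term, group 2: 0.3385. Group 1: 0.3329 at 6 months and 0.3273 at 12 months.
- 6 months: DID = 0.22 − 0.02 = 0.20. SE = √[1.036 × (0.3329/169.4 + 0.3385/150.6)] = 0.0661. Ratio 3.03.
- 12 months: DID = 0.25 − 0.02 = 0.23. SE = 0.0658. Ratio 3.50.
- Power, normal approximation: 85.7% and 93.8%.
- Power, noncentral t on 17 − 2 = 15 df: 80.8% and 90.4%.

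Logit, arcsine and SD = 0.5 scales at 320 give 79% to 85% at 6 months. With 22 patients per team (374), power is higher: 84% to 90% at 6 months. No variant using the stated ICC and serial correlation gives 71.4% and 83.1%. Setting the serial correlation to zero (normal, 320) gives 71.7% and 83.3%, but the text says 0.30.

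**4. Point-in-time power from the same inputs at 320.** 94.8% and 98.6% (normal) or 91.7% and 97.2% (t, 15 df), against the stated 80.8% and 90.4%. The stated pair instead matches the DID power by t in step 3.

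**5. Stated powers taken at face value.** Implied ratios are 1.960 + z(0.714) = 2.525 and 1.960 + z(0.831) = 2.918. Power to show both DIDs (bivariate normal):
- correlation 0: 0.714 × 0.831 = 59.3%
- correlation 0.3: 62.1%
- correlation 0.5: 64.3%
- correlation 0.7: 66.8%

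A correlation of 0.5 follows from a shared baseline with equal serial correlation. The upper bound at any correlation is the smaller power, 71.4%.

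**6. Size needed if 71.4% were correct.** Information must rise by (2.802/2.525)² = 1.23, so 320 × 1.23 ≈ 394 evaluable patients, ignoring the small rise in design effect.

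**7. Power for both DIDs if step 3 is right instead.** At correlation 0.5: about 82% from the normal figures, or about 76% treating the t-based powers as bivariate normal.

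**8. If either DID alone sufficed at 5%.** The chance of at least one false positive is 9.1% at correlation 0.5, and 1 − 0.95² = 9.75% if independent. Power for at least one, from the stated figures, is 0.714 + 0.831 − 0.643 = 90%.

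**The case against.** The strongest reply is that there may be no real shortfall. From the plan's own inputs the 6-month DID has 81% to 86% power at 320, so 71.4% may be the erroneous figure, or the two pairs may be mislabelled. This stands in part. The size of any shortfall is unknown, and 71.4% should not be treated as the trial's true power. But the mislabelling is only suggested, because other input sets match the same pairs. Whichever figure is wrong, the paragraph contradicts itself.

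A reader might also infer that the stated 5% error rate is wrong, or that success could be claimed on any of four results (two instruments at two times). The document supports neither. It states 5% per test and no family-wise rate. The testing text uses eCAP only. No section sets an any-result rule, and test order may sit in an analysis plan that is not shown. The joint hypothesis could also serve as a gatekeeper.

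Nor do the two harms add up. If both DIDs are required, the error rate is not inflated and only power suffers. If either suffices, the error rate rises to about 9% but power is at least 83.1%. What remains is that the article names two instruments and three hypotheses without saying which result decides.

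**Conclusion.** The power statement is wrong as written: 80% is promised for the primary hypotheses and 71.4% is reported for one of them. At face value, power for both DIDs is about 59% to 67% over correlations of 0 to 0.7, and at most 71.4%. This rests on the stated powers and on reading H1 as requiring both time points.

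The stated DID powers also do not follow from the stated inputs, which give about 81% to 86% and 90% to 94% at 320 evaluable patients. That result assumes proportion variances and the design effect applied to the whole DID variance. Neither 71.4% nor 83.1% should be carried forward without recomputation.

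The primary measure is described inconsistently and the deciding result is not stated. The 9% figure applies only if either time point alone would count as success, which the plan does not say.

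**What to change.** 1. Recompute power at 320 evaluable patients for the 6-month DID, the 12-month DID and both together from the stated ICC, serial correlation and rates. State the variance assumption and the reference distribution. Replace the 80% sentence with those figures, and correct the inputs or labels that do not match.
2. State that eCAP adherence (MAI) is the primary measure and ARMS is supportive.
3. State which DID result decides success: for example the 12-month DID first and the 6-month DID second in fixed order, or both required with the joint power reported. The choice is the sponsor's, and should be made before outcome data are examined.

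The cost is protocol wording and a registry update. The stated power may become less favourable, and ARMS loses co-primary status.
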